
**Fig. 2 Fig2:**
[figure not shown]
Seagram’s Lime Twisted Gin advertisement

Potential mediators and moderatorsThe following indicators are used as potential mediators:
*Cognitive elaboration (3 items)*. Participants will be shown the same advertisement as previously mentioned (Fig. 2) and asked to indicate on a 4-point Likert scale (1 = not much at all; 2 = a little; 3 = a good amount; 4 = a lot) the extent to which they (1) thought about the ad; (2) spent time thinking about the ad; and (3) paid attention to the advertisement (e.g., How much did you think about this advertisement?). This measure was adapted from Shiv et al. [49].*Counterarguing (4 items)*. Participants will be shown the same advertisement and asked to indicate on a 4-point Likert scale (1 = not much at all; 2 = a little; 3 = a good amount; 4 = a lot) the extent to which they (1) wanted to argue back to what it was saying; (2) thought of ways in which they disagreed with what was presented; (3) thought of ways that the information being presented was inaccurate or misleading; and (4) found themselves looking for flaws in the way information was presented in the advertisement (e.g., While viewing the ad, I sometimes felt like I wanted to “argue back” to what it was saying.). This measure was adapted from Moyer-Gusé and Nabi [50], α = 84.*Advertisement credibility (3 items)*. Participants will be shown an advertisement and asked to indicate on a varying 4-point Likert scale (e.g., 1 = unbelievable; 4 = believable) how (1) believable; (2) truthful; and (3) trustworthy they find the advertisement (e.g., This advertisement is unbelievable/believable.). Each Likert scale follows the above pattern. This measure was adapted from MacKenzie et al. [51].*Risk prototype: hook-up against will (14 items)*. Participants will be asked to indicate which of 14 adjectives describe a person who hooks up even if they were not sure that they wanted to (e.g., Imagine someone your age who hooks up even if they are not sure that they want to. How would you describe this person, using the following characteristics: prepared, confident, desperate, etc.?). This measure was adapted from Myklestad and Rise [52] α = .89.*Risk prototype: sex (14 items)*. Participants will be asked to indicate which of the same 14 adjectives describe a person who has sex with a boyfriend/girlfriend (e.g., Imagine someone your age who has sex with a boyfriend/girlfriend. How would you describe this person, using the following characteristics: prepared, confident, desperate, etc.?). This measure was adapted from Myklestad and Rise [52], α = .89.*Risk prototype: unprotected sex (14 items)*. Participants will be asked to indicate which of the same 14 adjectives describe a person who has unprotected sex (e.g., Imagine someone your age who has unprotected sex. How would you describe this person, using the following characteristics: prepared, confident, desperate etc.?). This measure was adapted from Myklestad and Rise [52] α = .89.

##### Student satisfaction

In terms of student (consumer) satisfaction, participants will be asked 7 items to indicate on 4-point Likert scales (e.g., 1 = not very much; 2 = a little bit; 3 = a lot; 4 = very much) how satisfactory the program is (e.g., How much did you learn from this program?). Participants will also be asked to open-endedly respond to three questions (e.g., What did you like best about the program?). Participants will be asked to indicate on a 4-point Likert scale (e.g., 1 = not likely at all; 2 = somewhat likely; 3 = likely; 4 = extremely likely) how likely they would be to recommend this program to a friend (e.g., How likely is it that you would recommend this program to a friend?). These measures were adapted from Scull et al. [34].

##### Fidelity of implementation

Process data will be collected to establish dosage. This data will include the start and end times that a user was in the program and which lessons they participated in. Process data do not include specific answers to any program questions.

#### Teacher measures

Teachers will complete a teacher questionnaire after program implementation to assess their satisfaction with the *Media Aware* program, Teacher Dashboard, and Teacher Training. The teacher questionnaire will consist of approximately 110 items and will cover demographics, program satisfaction, teacher training satisfaction, ease of implementation, program component use, and any suggestions for improvement.

### Statistical analyses

#### Preliminary analyses

Psychometric and descriptive analyses will be conducted to study the reliability, validity, and distributions of key variables. The impact of random assignment on producing equivalent groups between conditions will be evaluated using chi-squared analyses with the demographic characteristics. Missing data will be examined at each time point and handled with an appropriate imputation method, if necessary [53].

#### Outcome analyses

The immediate and short-term effectiveness of *Media Aware* for improving student outcomes will be examined using intention-to-treat analyses. Hierarchical linear modeling (with random intercepts at the school/teacher level) will likely be used to account for conditional nonindependence in outcome measures at posttest and follow-up using the SAS MIXED procedure and will examine multiple observations over time. An independent statistician will conduct interim analyses after all posttests are complete, and the PI and Co-Investigator (Co-I) will have access to the interim results. Given the minimal risk of the intervention, it is not anticipated that the trial will be terminated following these interim analyses. However, if the interim analyses suggest the possibility of any adverse effects of the trial on participants, the PI and Co-I will share the findings with the IRB chair and funder to determine how to proceed and whether or not the trial should be terminated. The PI and funder would make the final decision to terminate the trial, if necessary.

The model for the mean of each outcome will likely contain level 1 fixed effects representing the influence of (1) the student’s pretest score and (2) gender and level 2 fixed effects of condition. Student variables found to be nonequivalent between groups will be included as covariates in these models. The effect sizes will be calculated by dividing the appropriate contrast parameter by the sample standard deviation of the outcome. These analyses should reveal if there is a significant improvement in students’ sexual health and media outcomes after having received the program as compared with the delayed-intervention group. Follow-up analyses or structural equation modeling may be warranted. Qualitative analyses (media deconstruction skills) will be coded by research team members who will be blinded to intervention assignment. Unblinding will not occur.

Moderator analyses will examine subpopulations, likely defined by the three categorical variables of gender, relationship status, and prior sexual experience. These findings will provide evidence regarding how the effectiveness of the program varies as a function of student characteristics. Measures of program dosage and interactivity will be examined to see if differing quantity or quality of implementation can explain the findings. It is expected that results from this study will be prepared for publication in scholarly journals and updated in www.ClinicalTrials.gov.

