#### Randomization

Randomization will take place at the school level to avoid contamination effects. Each school and its participating classrooms will be assigned to either the intervention or the delayed-intervention group using an open label randomized controlled trial study design. Randomization may be stratified to balance groups between public or private schools, urban or rural schools, and the average socioeconomic status level of students in schools. The research team will use Excel’s random number generator function to randomize the schools to conditions. Randomization will take place after teachers provide informed consent and appropriate school approvals for conducting the study are obtained.

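### If posttest and follow-up are fitted jointly, the stated model has no within-student or school-by-time term: the change-over-time and moderator tests are miscalibrated, though the school-level condition test is not

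*Protocol article*

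**What the plan says.** All statements are in the protocol article.

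- **Random part** (Outcome analyses): "Hierarchical linear modeling (with random intercepts at the school/teacher level) will likely be used". One teacher takes part per school, so school and teacher form a single cluster level.
- **Repeated outcomes** (Outcome analyses): the model is to deal with nonindependence at posttest and follow-up "using the SAS MIXED procedure and will examine multiple observations over time".
- **Fixed part** (Outcome analyses): "The model for the mean of each outcome will likely contain level 1 fixed effects" for pretest score and for "gender and level 2 fixed effects of condition". No time or condition-by-time term is listed.
- **Further covariates** (Outcome analyses): "Student variables found to be nonequivalent between groups will be included as covariates in these models". This rule admits student variables only.
- **Design** (Randomization): "Randomization will take place at the school level to avoid contamination effects". Also, "Randomization may be stratified to balance groups between public or private schools, urban or rural schools", with the school's average socioeconomic level as a third possible factor.
- **Moderators** (Statistical analyses): gender, relationship status and prior sexual experience, all student characteristics.

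**The concern.** The article names the random effect, the fixed effects at both levels and the SAS procedure. It is therefore specific enough to be checked against the data it describes. Each student can contribute two outcome records, yet the only random term belongs to the school. A model fitted that way treats a student's two answers as independent given the school, and assumes that a school's level does not shift between waves beyond what condition explains.

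Two kinds of inference would suffer. The first is whether an effect seen at posttest persists at 3 months, which matters because the stated objective covers both immediate and short-term effectiveness. The second is whether the effect differs between kinds of student. Separately, school-level factors used to stratify randomisation would have no route into the model, so the precision that stratification buys would be lost.

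**Working it through.** **Inputs from the article.** 16 schools, 100 students per school, ICC .05, effect .40, power .80, alpha .05 (taken as two-sided).

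**Assumptions, because the article gives no figure.** Total variance is 1. Student-plus-residual variance is .95, split into student variance a and occasion variance b. Within-student correlation r = a/(a+b) is .3, .5 or .7. School-by-time variance v is 0 to .025. Outcomes are continuous. Cluster size m is 100, with 80 as a smaller alternative.

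**1. The article's sample size.** Design effect = 1 + 99 × .05 = 5.95. A noncentral t with schools-minus-2 df gives power .804 with 14 schools, .835 with 15 and .862 with 16. The stated figure of about 15 is reproduced. A normal approximation would need only 12.

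**2. Condition test, school intercept only.** Condition varies only between schools, so the estimated school variance absorbs the unmodelled student variance.
- Averaged over both waves, simulation with 14 df gives 4.8% to 5.5%, the same as after adding a student intercept.
- At a single wave, the ratio of model variance to true variance is 1 + (a/2m)/(.05 + .95/m). With r = .5 and m = 100 this is 1 + .002375/.0595 = 1.04. Simulated rejection is 4.1% to 5.0%.
- With school-by-time variance of .01 to .025 inside the total of .05, the 3-month test gives about 5.0% to 6.7% at 14 df.
- For reference, P(|t14| > 1.96) = 7.0%.

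**3. Condition by time, school intercept only.** For a school's mean change, the true variance is 2v + 2b/m. The model uses about 2(a + b + v/2)/m. Rejection = P(|Z| > 1.96 × √(model/true)).

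With v = 0 the ratio is 1/(1−r):

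| r | threshold | rejection |
|---|---|---|
| .3 | 2.34 | 1.9% |
| .5 | 2.77 | 0.6% |
| .7 | 3.58 | 0.03% |

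With r = .5 and v > 0:

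| m | v | true | model | ratio | rejection |
|---|---|---|---|---|---|
| 80 | .01 | .0319 | .0239 | .749 | 9.0% |
| 80 | .025 | .0619 | .0241 | .389 | 22.2% |
| 100 | .01 | .0295 | .0191 | .647 | 11.5% |
| 100 | .025 | .0595 | .0193 | .324 | 26.5% |

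Simulations agree. Taking formula and simulation together, the range is roughly 8% to 27%. Adding only a student intercept does not cure this: simulated rejection is then 17% at v = .005 and 26% at v = .01. By contrast, t tests on school-mean change stay at 4.6% to 5.8%.

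**4. Student-level moderators, school intercept only.** The model variance is (a+b)/2 where the truth is a + b/2, a ratio of 1/(1+r). Rejection = P(|Z| > 1.96/√(1+r)):
- r = .3: threshold 1.72, 8.6%
- r = .5: threshold 1.60, 11.0%
- r = .7: threshold 1.50, 13.3%

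Simulations with 20 to 100 students per school and 10% missing follow-up gave 10% to 13% for condition by gender at r = .5 and .7.

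**5. Stratification factor used but omitted.** Simulated rejection for condition, averaged over waves, is 2.7% if the factor explains 25% of between-school variance and 1.0% if it explains 50%.

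**The case against.** Joint fitting of the two waves is an inference. Student variables sit at level 1 and condition at level 2, no time term is listed, and posttest data are to be analysed alone at the interim. All of that also fits two separate pretest-adjusted models, for which a school intercept is enough. SAS MIXED also allows a within-student residual covariance, which is not a random intercept and need not appear in that parenthesis. The model wording is provisional, and covariance structure is often left to an analysis plan. These points stand, and they make the concern conditional. They do not remove it: the phrase about multiple observations over time reads more naturally as joint modelling, and the article gives no other model.

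Three stronger readings are tempting and not supported.
- **That ignoring repeated answers inflates the main treatment test.** It does not; step 2 of the working shows it near 5%.
- **That the plan uses a normal reference with 16 schools.** No degrees-of-freedom method is stated, and the sample size of about 15 is closer to a t-based calculation than to a normal one.
- **That known stratification factors are being ignored and error rises.** Stratification is only optional, and omission makes the condition test conservative.

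It is also true that condition-by-time is not listed as a planned test, and that the school-by-time variances are assumed.

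**Conclusion.** The concern holds in a limited form. If posttest and follow-up are fitted jointly with a school intercept alone, the comparison of effects between waves is badly calibrated. It is far too conservative without school-by-time variance (0.03% to 1.9% at r from .7 down to .3) and too liberal with a modest amount (roughly 8% to 27% for .01 to .025 at r = .5). The planned moderator tests are too liberal, at about 9% to 13%. The school-level condition test is sound with schools-minus-2 degrees of freedom. Omitted stratification factors cost precision only, and only if stratification is used. The sizes rest on assumed within-student correlation and school-by-time variance, neither of which the article gives. If each wave is modelled separately, the within-student part of the point falls away and only the stratification part remains.

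**What to change.** State whether the waves are analysed separately or jointly.

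- **If jointly:** add time and condition-by-time as fixed effects, an unstructured within-student covariance (REPEATED time within student), and random school and school-by-time effects. Take the posttest and 3-month contrasts, and their difference, from this model with Kenward-Roger degrees of freedom. The within-student covariance and the school-by-time effect are both needed, since a student term alone leaves the change-over-time test liberal. Fit the moderator interactions in the same model.
- **If separately:** say so. A school intercept then suffices at each wave.
- **In either case:** include as school-level fixed effects the stratification factors actually used.

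The cost is analysis wording. Three single-df stratification factors would take the condition test from 14 to 11 degrees of freedom. The critical t rises from 2.14 to 2.20, so intervals are about 3% wider (2.201/2.145 = 1.026) before the precision gained from the factors.

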### Ethics

#### Vulnerable population

Students in grades 9 and 10 will be recruited for this study using regulations set forth by the Health and Human Services Regulations regarding the Protection of Human Subjects. The study team will obtain parental permission for the students to participate in the research study, as well as student assent. The parent permission and student assent forms will be available in English and Spanish. Researcher and IRB Chair contact information will be printed on the forms in case parents or students have questions about the study.

#### Data and safety monitoring

To every extent possible, confidentiality will be assured to all participants. Project staff members are required to sign a confidentiality agreement immediately upon beginning employment. All project staff are required to complete training on the protection of human subjects in research. Participants will be given randomly assigned ID numbers to be used on the questionnaires. A separate linking list that includes names and ID numbers will be kept confidentially on a secure server that is only accessible to project members and the Systems Administrators (who are trained in the conduct of ethics research with human participants). After the project has ended and the data have been verified, the linking list will be destroyed, and the data will be rendered anonymous.

Research staff members will scan the incoming online questionnaire data on a regular basis and will be instructed to record any problems seen or concerns about any participants as noted from their responses. The PI will review and respond to these records immediately. Most data from the questionnaires are in the form of Likert scales, which means that participants cannot input anything other than a number response. However, some questions include open-ended fields. It is possible that participants might type identifying information (e.g., names) in the fields. If identifying information has been shared by the participant, it will be remedied immediately.

This is a minimal risk study, and we do not anticipate any study-related adverse events. However, any adverse events that occur will be evaluated and addressed by the PI and study team and reported to the IRB promptly. Serious adverse events (SAEs) will be evaluated within 24 h, and any other anticipated problems or events will be evaluated within 72 h; reporting to the IRB will occur within 2 weeks. If the research staff becomes aware of an SAE, the PI will provide written documentation of the SAE to the IRB Chair. The IRB Chair will provide a report of the SAE and its resolution to both the NIH Program Officer and the PI.

## Discussion

It is important that sexual health education programs be rigorously evaluated to ensure that they are effective in enhancing student health. The program being evaluated in this study, *Media Aware*, has the potential to be an innovative evidence-based program that high schools can implement to promote adolescent sexual and relationship health. In addition, this program has the potential to enhance adolescents’ critical thinking about media messages. The study design, specifically including students’ data collection at three time points (pretest, immediate posttest, and 3 months follow-up), allows for evaluation of the immediate effects of the program on student outcomes, as well as any behavioral effects that may occur during the 3 months after the students receive the program. In addition, this study will gather student and teacher feedback on the program, which will help determine the likelihood of program adoption by schools.

### Potential barriers to study recruitment

There are a few potential barriers to study recruitment. First, it can be difficult to obtain school approval to allow research studies to take place. District or school policy may not allow research studies to be conducted in the schools, and some do not allow the collection of data pertaining to sexual health, specifically. If research is permitted in schools, there may be a rigorous approval process, which includes demonstrating that the research will not cut into instructional time. Schools will be informed that this program can be used as a substitute for other sexual health education lessons and should take less time to complete than traditional sexual health education programs.

Second, some schools require a period during which parents can review a sexual health education curriculum prior to it being taught in the classroom. Parental review of traditional print materials often requires parents to come to the school or district offices to review the curriculum materials, which can be a burden on parents, particularly if they are working and have to visit the school during the workday. Furthermore, there is no way for parents to know exactly how a teacher-led program will be implemented in the classroom (e.g., teachers could add their own content or opinions). The self-contained, web-based nature of *Media Aware* is expected to streamline the parental review process by allowing teachers to send parents a link to the program via an email for review. Furthermore, parents can be assured that the content they review is exactly what their child will be exposed to in class.

Third, schools may also decline to allow this research study to be conducted in their school because changing a school curriculum may elicit teacher pushback. Implementing a new program may require additional effort on the part of their teachers. Teachers have limited class time in which to cover material mandated by the state and school district, and they may view learning a new curriculum as a difficult task. However, given the web-based nature of *Media Aware,* teachers do not have to teach a new curriculum. This feature of utilizing web-based program delivery should minimize teacher resistance to implementing a new curriculum.

### Study strengths and limitations

There are many strengths to the study design. The study is designed as a randomized controlled trial, a rigorous design for program evaluation. Randomization will increase the likelihood that the intervention group and delayed-intervention group are evenly balanced with respect to many characteristics like student diversity and socioeconomic status of the students in the school district. Because only one teacher per school will be participating in the study, there will be little chance of cross contamination between groups. Participating teachers and students from one school will likely have little to no contact with teachers and students in another school. Because the questionnaires will be completed during school hours, study attrition is minimized.

### Implications for the field

This study has many implications for the field of sexual health education. This study will evaluate the feasibility and efficacy of using web-based programming to deliver comprehensive sexual health and media literacy education (MLE) to promote students’ sexual health outcomes. There are few, if any, evidence-based comprehensive sexual education programs for high school students that use an MLE approach, and, to the best of our knowledge, none that used a web-based format to deliver content. Additionally, this program expands the definition of comprehensive sexual health to include topics such as gender, consent, healthy relationships, and communication with partners, parents, and medical providers.

